**Methods/design:**

The EASE study is a hybrid Type 1 effectiveness and implementation trial. The effectiveness trial is a parallel two-armed multicenter randomized controlled add-on superiority trial, enrolling individuals who receive support from psychosocial crisis teams within 7 weeks after trauma. Participants are randomized to CIPE + treatment as usual (TAU) or TAU only. The primary outcome is the level of PTSD symptoms 6 weeks after randomization (10–13 weeks post trauma). Secondary outcomes include symptoms of depression and insomnia, quality of life, and CIPE cost-effectiveness. The implementation trial examines policy-level factors influencing CIPE implementation, using the Exploration, Preparation, Implementation, Sustainment framework.

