### Aims and hypotheses

The study hypotheses and research questions are presented in Table 1. The primary aim is to examine the effectiveness of CIPE, delivered approximately 1 to 2 months after a trauma, as an indicated secondary prevention aimed at reducing PTSS and the incidence of PTSD. We will compare the effect of CIPE + treatment as usual (TAU) vs. TAU only, to examine whether CIPE has the potential to improve the ordinary psychosocial services provided by crisis teams. In such contexts, TAU (see “TAU” under the section “Interventions”) is considered to be an appropriate comparator with several benefits [26, 27]. TAU reflects the current real-world practice of the psychosocial crisis teams against which any added benefit of CIPE must be demonstrated, in order to evaluate if CIPE improves standard care and should be routinely implemented in Norwegian municipalities. The study was designed as an add-on trial (i.e., CIPE as an add-on) due to practical and ethical considerations.

**Table 1 Tab1:** Hypotheses and research questions in the EASE study

Hypotheses concerning the effectiveness and cost-effectiveness of CIPE	
H1	Participants receiving CIPE + TAU will have significantly less PTSS than participants receiving TAU at 6 weeks post T1, and at 6 and 12 months after the traumatic incident
H2	Significantly fewer participants receiving CIPE + TAU will fulfill the criteria for PTSD compared to participants receiving TAU, at 6 and 12 months post trauma
H3	Participants receiving CIPE + TAU will have significantly less symptoms of depression and insomnia than participants receiving TAU at 6 weeks post T1, and at 6 and 12 months after the traumatic incident
H4	Participants in the CIPE + TAU-condition will report significantly higher treatment satisfaction at post-treatment, compared to those in the TAU-condition
H5	Participants with traumatic loss receiving CIPE + TAU will have significantly less symptoms of prolonged grief than participants with traumatic loss receiving TAU 12 months after the loss
H6	Fewer participants in the CIPE + TAU-condition will be referred to second-tier specialty mental health services, and more will achieve improved quality of life within the first year after the traumatic incident, compared to participants in the TAU-condition
H7	The CIPE + TAU implementation is more cost-effective compared to TAU in the short run and may even dominate TAU in the long run (i.e., more effective and less costly)

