### Data collection

Figure 2 presents the trials’ enrollment, intervention, and measurement schedule. Participants enrolled within 3 weeks after the incident are assessed with self-report measures at the time of enrollment (T0). All participants are subsequently assessed before randomization (T1), post-treatment (T2), and at 6-month (T3) and 12-month (T4) follow-ups. The main outcome will be measured at post-treatment (T2). Self-report data from participants are collected using an electronic survey solution offered by BASS at the Karolinska Institute, Stockholm. The same system is used to obtain written informed consent and to deliver CIPE. Links to questionnaires are sent to responders using SMS and email. Data from the therapists are collected using Nettskjema and Services of sensitive data (TSD) at the University of Oslo (see “data management and storing”). The research coordinator monitors the data collection process and sends reminders to reduce attrition rates.

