### Statistical analyses

H1–3 are tested with linear mixed effects models. The linear mixed effects model includes fixed effects for treatment group (intervention vs. control) and time (post-intervention, 6 and 12 months). In a hierarchical setup, a second step includes a treatment × time interaction. Random effects include random intercepts for participants to account for individual differences. The mixed effects models are applied using the R package nlme [70]. H4–6 are examined using independent t-tests. The quality-of-life change (change in QALY) of participants in CIPE vs. TAU (H6) is analyzed using the mixed effects model. Estimation is conducted using restricted maximum likelihood, with all available observations included, yielding unbiased estimates under the assumptions of missing at random or missing completely at random. For the t-tests, missing data are handled using multiple imputation.

Hypothesis 7 involves a comprehensive economic evaluation comparing the cost-effectiveness of CIPE relative to TAU in terms of both costs and consequences/effectiveness [71]. Costs are assessed using the ingredients approach, which involves three steps: first, identifying each resource required for the intervention; then, measuring these resources; and finally, valuing them. The effectiveness of the intervention is measured by QALY—a composite measure combining both quantity of life (mortality) and quality of life (morbidity) into a single metric [72]. For each arm, mean costs and mean QALYs are estimated across all participants to calculate the incremental cost (ΔC) and incremental effect (ΔQALY). The incremental cost-effectiveness ratio (ICER) or incremental cost per incremental QALY (ΔC/ΔQALY) is then calculated for decision-making. To accept the intervention, ICER should be less than the willingness-to-pay or cost-effectiveness threshold. Since there is no official threshold in Norway, we apply a threshold recommended by the Norwegian Directorate of Health (NOK 500 000 at 2005 prices), adjusted to current price levels [73].

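### The tests described for H1 are a three-visit average and a change in effect between visits; the plan does not make the T2 contrast the primary test

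*Protocol article*

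**What the plan says.** The endpoint is set at a single time. The abstract (Methods/design) states: "The primary outcome is the level of PTSD symptoms 6 weeks after randomization". The Data collection section repeats it: "The main outcome will be measured at post-treatment (T2". The Assessments section gives the PCL-5 as the instrument.

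H1 in Table 1 is wider. It says that the CIPE + TAU group "will have significantly less PTSS than participants receiving TAU at 6 weeks post T1, and at 6 and 12 months after the traumatic incident". No order or priority among the three times is given.

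The Statistical analyses section tests H1 to H3 with a linear mixed model containing "fixed effects for treatment group (intervention vs. control) and time (post-intervention, 6 and 12 months". It continues: "In a hierarchical setup, a second step includes a treatment × time interaction". On the covariance it says: "Random effects include random intercepts for participants to account for individual differences". The baseline visit T1 is not among the listed time levels. The section does not say whether time is categorical, which level is the reference, which coefficient answers H1, or what the two-step build is meant to decide.

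**The concern.** A group-by-time interaction is often read as the treatment benefit. That reading needs baseline to be one of the time levels. Here every level is after randomization, so a benefit that is real and equal at all three visits produces no interaction. The treatment term from step 1 mixes the T2 effect with effects at 6 and 12 months.

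If either p-value is taken as the result for the primary outcome, two things can go wrong. An effect that is present at T2 and then fades can be missed. An effect that appears only later can be reported as success on an endpoint where there was none. Because the primary test is not fixed, there are also several candidate p-values for one primary claim.

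**Working it through.** **The plan's own figure.** The Power section gives d = 0.3, 95% power, alpha 0.05 and 150 participants (at least 73 per group). For a two-sided comparison of two means at one visit, d = 0.3 with 95% power needs 289 per arm; 73 per arm is what d = 0.6 needs. The stated size therefore does not follow from the stated inputs for a T2 contrast. That is a separate matter. Below I use the plan's 75 per arm and d = 0.3 only to compare the candidate tests.

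**What each term estimates.** One large data set was simulated (2000 per arm, within-person correlation 0.5) with true benefits of 0.30, 0.15 and 0.00 SD at T2, 6 and 12 months.
- Step 1 (treatment + time): treatment coefficient −0.153. The true average is (0.30 + 0.15 + 0.00)/3 = 0.15.
- Step 2 (interaction added, categorical time, T2 as reference): treatment coefficient −0.307, equal to the raw T2 mean difference. The interaction coefficients, 0.158 and 0.305, are the changes from T2 to the later visits.

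**Inputs for the comparison.** n = 75 per arm and d = 0.3 (Power section); random intercept, hence equal correlation r between visits (Statistical analyses). Assumed, because not stated: r from 0.3 to 0.7, two-sided 0.05, complete data, SD = 1, no baseline adjustment.

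**Formulas.**
- Step-1 term: SE = √[(2/n)(1 + 2r)/3]. At r = 0.3 this is √(0.02667 × 0.5333) = 0.119; at r = 0.7 it is √(0.02667 × 0.8) = 0.146. For effects 0/0.3/0.3 the average is 0.2. Then 0.2/0.119 = 1.68 and 0.2/0.146 = 1.37, giving rejection rates of 39% and 28%.
- Interaction: F test on 2 and 296 df, with noncentrality Σ(effect − average)² / [(1 − r)(2/n)]. For 0/0.3/0.3 the sum is 0.04 + 0.01 + 0.01 = 0.06, giving 3.2 at r = 0.3 and 7.5 at r = 0.7. A constant effect gives 0.
- T2 contrast: SE = √(2/75) = 0.163, and 0.3/0.163 = 1.84, giving 45% power.

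**Rejection rates at 75 per arm** (r = 0.3 first, then r = 0.7)

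| True effect at T2/6m/12m | Step-1 term | Interaction | T2 contrast |
|---|---|---|---|
| 0.3/0.3/0.3 | 71–54% | 5% | 45% |
| 0.3/0.15/0 | 24–18% | 26–55% | 45% |
| 0.3/0/0 | 13–11% | 34–68% | 45% |
| 0/0.3/0.3 | 39–28% | 34–68% | 5% |

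**At 180 per arm** (the 360 recruitment target, before attrition) the gap widens. With no T2 effect and 0.3 later, step 1 rejects 74–56% and the interaction 70–97%. With 0.3 at T2 only, step 1 has 25–19% power against 81% for the T2 contrast. With a constant 0.3, step 1 has 97–89% against 81%.

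**The case against.** A reader might infer that the stated model cannot test the primary endpoint at either step. The document does not support that. With categorical time and T2 as reference, the treatment coefficient of the step-2 model is exactly the T2 difference. Listing three discrete visits suggests categorical time, and listing post-intervention first suggests T2 as reference. This stands, and it means that no new model is needed. It does not settle the matter: the text states neither the coding nor the coefficient, and the reference level depends on how the visits are labelled. Sorted alphabetically, labels beginning with 12, 6 and post would make 12 months the reference.

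A reader might also infer that the plan has chosen the wrong decisive test. It has not chosen one. The harm described arises only if the step-1 or interaction p-value is taken as the answer for T2.

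Nor is step 1 always the weaker test. Under a constant effect it is the stronger one, and the Background reports that effects in the earlier CIPE trial held to 6 months, which favours that pattern. The same section says that most exposed people recover naturally, so a fading difference is plausible too. Nothing in the document points to an effect that is absent at T2 and present later; that row only shows what the tests respond to.

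H1 covers all three times, so a model across visits is a reasonable way to address H1 as a whole. It does not replace a test at the single time declared primary.

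Finally, a full protocol or SAP may already name the contrast, and an article may leave such detail to it. But the article is not merely brief here. It sets out a specific two-step procedure, and the two tests that it describes do not target its own endpoint.

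**Conclusion.** The point holds in this form: the primary outcome is PCL-5 at T2, the described steps test an average effect and a change in effect, and the T2 contrast that the step-2 model contains is not made the primary test. The step-1 and interaction tests are valid for their own hypotheses; the fault is in reading either as the result at T2.

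At 75 per arm, step 1 rejects 28–39% of the time when the T2 effect is zero and the later effects are 0.3. It has 11–13% power when the effect is 0.3 at T2 only, against 45% for the T2 contrast. Under a constant 0.3 it has 54–71% against 45%, and the interaction stays near 5%. What each term estimates follows from the model as written. The percentages rest on the assumed correlation, complete data, two-sided testing and no baseline adjustment. The matter should be settled before analysis because it determines the trial's main claim.

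**What to change.** State that the primary test is the CIPE + TAU minus TAU contrast in PCL-5 at T2, two-sided at 0.05 with a 95% confidence interval, from the mixed model with treatment, categorical time (T2, 6 and 12 months) and their interaction. State that it is carried out whatever the interaction test shows. Report the 6- and 12-month contrasts from the same model as secondary. The two-step build may stay as description, but it should not decide H1.

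This takes two sentences in the analysis section or SAP and needs no new data or model. Recruitment is expected to run to September 2026 (Trial status), so it can be fixed before analysis. The cost is some power if the effect is constant: 45% against 54–71% at 75 per arm, or 81% against 89–97% at 180 per arm.

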## Method

### Research context

Twenty-one municipal crisis teams from the central-eastern parts of Norway participate in the study. The crisis teams are chosen to deliver the intervention due to their aforementioned role in the Norwegian health care system and the well-organized psychosocial services already offered by these teams. Participation requests were directed to municipal crisis teams by the Regional Resource Center for Violence, Traumatic Stress, and Suicide Prevention (RVTS East) to ensure variation in municipal population size, and municipalities from both rural and urban areas. A list of study sites is available in the trial registration (ClinicalTrials.gov identifier: NCT06592677).

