### Randomization

Eligible participants are randomized 1:1 in random block sizes of 4, 6, or 8 to either CIPE + TAU or TAU only, using the Sealed Envelope software [36] at T1. To mitigate the risk of contamination across treatment conditions, participants from the same household are cluster-randomized. The randomization is stratified on the level of municipal crisis teams to ensure an even distribution of cases in each treatment condition across municipalities. An independent, blinded senior researcher is responsible for all randomization procedures. The allocation is revealed to the study coordinator only after the T1 assessment and decision of inclusion are completed.

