### Power and sample size calculations

Previous CIPE studies report effect sizes within the range of *d* = 0.6–0.8. For the primary hypothesis in this study, a more conservative effect size of *d* = 0.3 is expected. With 95% power and an *α*-level of 0.05, 150 participants (73 in each group minimum) are required to detect a significant between-group effect. Consequently, assuming a 20% data attrition rate, at least 183 participants should be recruited. The municipal crisis teams involved in the study currently cover approximately 1,080,000 inhabitants. Although official statistics on the number of traumatic events handled by these teams are lacking, based on the best unofficial statistics available, a conservative estimate suggests 0.5 to 1 case per 1000 inhabitants annually. With a cautious estimate of 0.5, and with each incident involving a mean of two victims aged 16 or older, about 2150 victims are eligible for recruitment over 2 years. Moreover, we assume a ~50% response rate [75] and that approximately 30% have PTSD symptoms 1 month after the incident [76]. These parameters result in a sample of 360 participants, which constitutes the recruitment target. Assuming an overall attrition rate of 40%, 216 participants will complete the 12-month follow-up assessment.

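### Households are randomised as clusters within crisis-team strata, but the stated analysis and sample size ignore them, so type I error may exceed 5% by an amount the documents cannot fix

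*Protocol article*

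**What the plan says.** Under Randomization, the protocol article states that "participants from the same household are cluster-randomized", to limit contamination between arms, and that "The randomization is stratified on the level of municipal crisis teams". The section Research context gives the number of strata: "Twenty-one municipal crisis teams from the central-eastern parts of Norway participate in the study".

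Under Statistical analyses, the model for H1 to H3 is described in two parts. The fixed part is "The linear mixed effects model includes fixed effects for treatment group (intervention vs. control) and time (post-intervention, 6 and 12 months"; a treatment-by-time interaction is added in a second step. For the random part: "Random effects include random intercepts for participants to account for individual differences". H4 to H6 are assigned to independent t-tests with multiple imputation, except that the H6 change in quality of life goes to the mixed model. No household or crisis-team term appears.

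Power and sample size calculations asks for 150 participants, or 183 after attrition, with no allowance for clustering. Its recruitment forecast works "with each incident involving a mean of two victims aged 16 or older".

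**The concern.** Two people from the same household receive the same arm by design, and they will often have been exposed to the same event. For them the household, not the person, is the unit of randomisation. A participant random intercept handles repeated measurements on one person. It does nothing for correlation between two people in one household. An independent t-test assumes that this correlation is absent.

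If household members resemble each other on the PCL-5 or the other outcomes, the treatment contrast varies more than the model believes. Confidence intervals are then too narrow and the test rejects too often under the null. A larger sample does not cure this, because the ratio of true to reported standard error does not shrink with the number of participants.

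The stratification factor is also missing from the model. That is a separate fault with the opposite sign: the balance that stratification achieves is not credited, so the standard error is too large and precision is lost.

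**Working it through.** **The plan's own figure.** The stated 150 (73 per arm minimum) includes no household design effect. It also does not follow from the stated inputs: d = 0.3, 95% power and two-sided 5% (sidedness is not stated) need 289 per arm, while 73 per arm corresponds to d = 0.6. That is a separate matter. Here 150 serves only as the base to which a design effect is applied. The 183 equals 146/0.8 = 182.5, rounded up.

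**Assumed inputs, because the documents give none.** Let s be the mean number of other co-randomised household members per participant, and ICC the within-household correlation of the outcome.

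- Low end, s = 0.15: the plan assumes about 50% response and about 30% with symptoms. If both victims of a two-victim incident share a household and take part independently, s = 0.5 × 0.3 = 0.15. The plan gives two victims per incident, not per household, so s could be lower. Families who decide jointly would push it up.
- High end, s = 1: every participant belongs to a pair.
- ICC from 0.05 to 0.5.

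**Formulas.** DE = 1 + s × ICC. The reported standard error is 1/√DE of the true one. The actual level of a nominal two-sided 5% test is 2 × (1 − Φ(1.96/√DE)).

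| s | ICC | DE | SE understated by | Actual level | 150 becomes |
|---|---|---|---|---|---|
| 0.15 | 0.05 | 1.008 | 0.4% | 5.09% | 152 |
| 0.15 | 0.3 | 1.045 | 2.2% | 5.52% | 157 |
| 0.3 | 0.3 | 1.09 | 4.2% | 6.05% | 164 |
| 0.5 | 0.3 | 1.15 | 6.7% | 6.76% | 173 |
| 1 | 0.3 | 1.30 | 12.3% | 8.56% | 195 |
| 1 | 0.5 | 1.50 | 18.4% | 10.95% | 225 |

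Applied to 183, the same extremes give 185 to 275.

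**Both omissions together.** The formula covers households only. A simulation therefore allocated households in blocks within 21 strata (the plan: "Eligible participants are randomized 1:1 in random block sizes of 4, 6, or 8") and applied an unadjusted t-test to participant means. With complete data this equals the treatment main-effect test of a participant-random-intercept model. There were 8,000 replicates per setting, with a Monte Carlo standard error of about 0.25 percentage points near 5%.

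| s | Household ICC | Team ICC | Level, N = 150 | Level, N = 360 |
|---|---|---|---|---|
| 0 | 0 | 0.05 | 4.6% | 4.4% |
| 0 | 0 | 0.10 | 4.2% | 4.1% |
| 0.15 | 0.2 | 0.05 | 4.6% | 5.0% |
| 0.15 | 0.3 | 0.05 | 5.0% | 5.1% |
| 0.3 | 0.3 | 0.05 | 5.5% | 5.8% |
| 1 | 0.3 | 0.05 | 8.4% | 8.4% |
| 1 | 0.5 | 0.05 | 11.0% | 10.3% |

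Omitting teams alone is conservative. With few pairs the two omissions roughly cancel. With mostly paired households the inflation dominates, and it is much the same at 360 as at 150.

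**The case against.** The strongest reply is that the effect may be negligible. The documents do not say how many households contribute more than one participant. With few of them, the level stays near 5% even when the strata are ignored as well. This stands, and it rules out saying that type I error does exceed 5%. It does not rescue the plan: two omissions that happen to offset each other are no safeguard, and adding crisis team alone, a common correction, would remove the offset and leave the household inflation.

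A second reply is that the article says the random effects include participant intercepts, which does not strictly exclude others, and that covariate detail is often left to a statistical analysis plan. For crisis team this has some force. For households it has less. The article names fixed effects, random effect, software, estimation method and missing-data handling, and an independent t-test cannot accommodate clusters under any reading.

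A third reply is that the recruitment target of 360 leaves room. In headcount it does: even DE = 1.50 turns 183 into 275. Numbers do not correct a standard error that is too small.

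Three stronger inferences are tempting but unsupported:

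- A reader might conclude that concealment fails for a household member who reaches T1 after a relative was allocated. The article says "The allocation is revealed to the study coordinator only after the T1 assessment and decision of inclusion are completed" and does not say that members are allocated one after another. Its text is compatible with allocating a household once all its members have completed T1.
- A reader might expect H5 to suffer most, because several members of one household may grieve the same death. That is plausible, but the article defines the group only as participants with traumatic loss, and nothing allows the effect to be sized.
- A reader might blame the missing strata for false positives. Their omission acts in the other direction.

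**Conclusion.** The stated analysis does not match the stated randomisation. With any positive within-household correlation, the household omission makes standard errors too small, so type I error may exceed 5%. The size cannot be determined from the documents. Under the assumed ranges it is about 5.1% to 11% for households alone. When few households are paired and the omitted strata offset it, it is about 4.6% to 5.1%. These figures rest on assumed household shares and correlations, a two-sided test and, in the simulation, equally likely teams and complete data. The mismatch is certain; its numerical consequence is not. It is worth correcting because the remedy is cheap and protects the conclusions whichever case turns out to apply.

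**What to change.** - **H1 to H3 and H6 quality of life:** add a random intercept for household, with participants nested in households and single participants as clusters of one, or use household-cluster-robust standard errors. Adjust for crisis team as a random or fixed effect. The chosen R package, nlme, supports nested random intercepts.
- **Remaining H4 to H6 comparisons:** replace the t-tests with regressions that include crisis team and use household-robust standard errors, fitted within the multiple imputation already planned.
- **Reporting:** give the number of households with more than one participant, and state in the power section that no household design effect was included.
- **Sensitivity analysis:** exclude any participants who completed T1 after a member of their household had been allocated, if there are any.

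The cost is analysis wording plus the registry update and ethics submission that the article prescribes for revisions. The trial statistician is blinded and recruitment is estimated to end in September 2026, so the change can be made without knowledge of results. The downsides are slightly wider intervals and, if few households are paired, a poorly estimated household variance component; robust standard errors suffice in that case. No change to when households are randomised is asked for: in a trial recruiting since September 2024 that would be a procedural amendment, and the documents do not show that it is needed.

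### The only covariance element named for T2–T4 is a participant random intercept, so the T2 contrast's standard error could rest on a variance pooled over all three visits

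*Protocol article*

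**What the plan says.** Under Statistical analyses, H1 to H3 are tested with linear mixed models. The fixed effects are treatment group and time, and time has three levels: post-intervention, 6 months and 12 months. The interaction comes later: "In a hierarchical setup, a second step includes a treatment × time interaction". On covariance the article says: "Random effects include random intercepts for participants to account for individual differences". On software it says: "The mixed effects models are applied using the R package nlme". No random slope, residual correlation structure or visit-specific variance is mentioned.

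Estimation is by restricted maximum likelihood, "with all available observations included, yielding unbiased estimates under the assumptions of missing at random or missing completely at random".

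Three other places bear on this:

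- Data collection makes T2 the visit for the main outcome.
- Trial design puts T2 at 10–13 weeks after trauma, with follow-ups at 6 and 12 months after the event.
- Power and sample size calculations states: "Assuming an overall attrition rate of 40%, 216 participants will complete the 12-month follow-up assessment".

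**The concern.** A random intercept with independent, equal-variance residuals implies compound symmetry: one variance for every visit and one correlation for every pair of visits. The gaps here are unequal. Taking 6 months as about 26 weeks, they are about 13–16 weeks from T2 to T3 and about 26 weeks from T3 to T4. The sample is also expected to be a mix of people who recover and people who do not. Neither constant variance nor equal correlation can be taken for granted.

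Two results are exposed. First, the p-value and interval for the T2 contrast could be too narrow or too wide, because its standard error would borrow the spread seen at T3 and T4. Second, likelihood estimates are protected under missing at random only when the covariance is modelled adequately. The article states the protection without that condition, while planning for 40% attrition by 12 months.

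**Working it through.** **Plan figure.** 360 × (1 − 0.40) = 216, so the completer count reproduces. The article gives no PCL-5 SD or between-visit correlation. All SDs and correlations below are therefore assumptions.

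**T2 contrast, complete data, arm × visit means.** With n per arm:

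- correct standard error = SD(T2) × √(2/n)
- random-intercept standard error = √(mean of the three visit variances) × √(2/n)
- ratio r = √(mean variance / T2 variance)
- actual two-sided error = 2 × [1 − Φ(1.96 r)]

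Correlations do not enter r. With 75 per arm (150 in total, from the sample-size section), √(2/75) = 0.1633. For SDs 16/14/12 the variances are 256, 196 and 144, with mean 198.67. The model standard error is 14.09 × 0.1633 = 2.30 and the correct one is 16 × 0.1633 = 2.61, so r = 0.881.

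| Assumed SDs T2/T3/T4 | r | Error, formula | Error, 20,000 simulated null trials |
|---|---|---|---|
| equal | 1.000 | 5.0% | not run |
| 15/14/13 | 0.935 | 6.7% | 7.0% |
| 16/14/12 | 0.881 | 8.4% | 8.7% |
| 12/14/16 | 1.175 | 2.1% | 2.5% |

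A second set, scaled to a T2 SD of 1, gives the same picture:

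- 1/0.95/0.9: 6.2%
- 1/0.9/0.8: 7.7%
- 1/0.85/0.75: 8.7%
- 1/1.1/1.2: 3.1%

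Simulation at N = 146 (2 × 73), with decaying correlations and dropout depending on observed scores, gave 7.9% for 1/0.9/0.8, 9.6% for 1/0.85/0.75 and 3.1% for 1/1.1/1.2. When compound symmetry was true it gave 4.7%. With 1,500 trials the simulation error near 8% is √(0.08 × 0.92 / 1500), or about 0.7 percentage points.

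**Step-1 pooled effect, complete data.** This effect compares participant means over the three visits. Take SDs 16/14/12 with assumed correlations of 0.75 for T2–T3 and T3–T4 and 0.50 for T2–T4. The covariances are 168, 126 and 96. The true variance of a participant mean is (596 + 2 × 390)/9 = 152.9. Compound symmetry uses the average variance, 198.67, and the average covariance, 130: (198.67 + 2 × 130)/3 = 152.9. The two agree, so the test keeps its size. Simulated error was 5.2% (16/14/12), 5.1% (15/14/13) and 4.9% (12/14/16).

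**12-month contrast.** This was a large-sample comparison with a true effect of 0.30 T2-SD units, T2 complete, and later dropout depending on earlier scores.

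- *Dropout related to symptoms alike in both arms.* The random-intercept estimate lies between 0.30 and 0.31, so the bias is about 0.01 SD or less.
- *Dropout related to symptoms differently by arm, with declining SDs (1/0.9/0.8 and 1/0.85/0.75).* The random-intercept estimate is about 0.35 with 25% missing and about 0.38 with 39% missing. An unstructured covariance gives 0.30 in each case.
- *Same arm-dependent dropout, but compound symmetry true.* The random-intercept estimate stays at 0.30.

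The material bias is therefore 0.35 − 0.30 = 0.05 to 0.38 − 0.30 = 0.08 SD. It needs both a wrong covariance and arm-dependent dropout.

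**The case against.** A participant random intercept is a conventional model, and a condensed article may leave the residual structure to the full protocol or analysis plan. The text says that the random effects include this intercept. It does not say that nothing else is modelled, and nlme can fit the richer structures. A reader might infer that the plan rules out unequal variances. The wording does not support that, and this part of the objection stands.

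The missing SDs also matter. A reader might conclude that the primary test is anti-conservative. The documents do not show this. Background describes mostly resilience or recovery, with about one in five on sustained or delayed-onset courses. Such a mixture could narrow or widen the spread, so the direction is unknown. Unequal spacing bears on the correlations and does not change the complete-data T2 ratio.

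The step-1 effect keeps its size with complete data, and the article does not say which term provides the T2 test. The distortion therefore belongs only to a T2 contrast taken from step 2.

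Finally, the 40% attrition figure might be read as showing that the 12-month result will be biased. It is an overall planning assumption and says nothing about dropout differing by arm. With similar dropout in both arms the bias is negligible.

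The core of the point remains. The article does more than leave a detail open: it names a concrete model, estimator and package, and claims unbiasedness for it. Run as written with the package defaults, the model imposes a restriction that the article does not justify.

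**Conclusion.** The point holds in conditional form. As written, with default residuals, the model assumes equal variance and equal correlation over T2–T4. A T2 contrast from the step-2 model would then have a two-sided error of about 5% if SDs are equal, about 6–9% if they fall over time, and about 2–3% if they rise. These figures rest on assumed SDs. If variances and correlations are roughly equal, the stated model is adequate.

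The missing-at-random statement is incomplete because it omits the need for an adequate covariance model. The 12-month consequence is limited to the combination described above and concerns a time point that is not primary. This is a worthwhile, low-cost improvement to the primary analysis and does not show that the planned result will be wrong.

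**What to change.** State that the outcome model contains arm, visit and arm × visit, with an unstructured within-participant covariance over T2, T3 and T4, fitted by restricted maximum likelihood. In nlme this is corSymm for the correlations plus varIdent by visit. The unstructured matrix takes the place of the participant random intercept. Any household or crisis-team random effect can stay on top. Name the T2 contrast from this model as the primary test, and name heterogeneous compound symmetry as the fallback if the fit does not converge. Add to the missing-data sentence that the property depends on an adequately specified covariance.

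The cost is one line of model specification in the package already chosen. Six covariance parameters replace two (6 − 2 = 4 more), which is small for 150 or more participants at three visits. Convergence failure should be rare and is covered by the fallback. Trial status puts the end of recruitment at September 2026, and Blinding says that the trial statistician is blinded, so the change can be fixed before unblinding.
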